### Data collection

Data collection is conducted by field workers specifically employed for assessment of trial outcomes; this team is separate from the personnel implementing the intervention. Data collection comprises biospecimen sampling at both the settlement and household levels, field data measurements and household surveys. Specimen collection involves blood and faeces from children under the age of 5 years; environmental soil, water and animal scat samples; and vector trapping, with intended sampling frequency as shown in table 2. Ecological field data assessment involves continuous passive acoustic monitoring, temperature logging and flood assessment including the use of satellite imagery. Anthropometric measures are taken annually among children under the age of 5 years. Surveys are administered quarterly, with different modules asked of varying-aged participants to assess physical health, healthcare utilisation, psychological well-being, financial well-being, time-use and perceptions of social cohesion and collective efficacy. Questions regarding household level data (ie, household member composition, flooding) are administered preferentially to the adult female head of household and questions regarding children under the age of 15 years are preferentially directed to the adult caregiver who has seen them most days in the past 7 days. Questions regarding adult health and well-being, financial well-being, time-use and perceptions of social cohesion and collective efficacy are preferentially administered to: (1) primary caregivers where households contain children under 15 years, and (2) female or (3) male heads for households with no children. If the preferred respondent is not at home, field teams attempt two re-visits. To maintain participation over the trial period and to show appreciation for the time spent by participants on study-related activities, we will provide small culturally appropriate gifts of nominal value, as recommended by our in-country partners.

**Table 2 T2:** Data collection tools and specimens for primary and secondary outcomes

	Minimum frequency			
**Primary outcomes**	C	Q	B	A
Faeces collection, children <5 years of age for: Prevalence, diversity and concentration of bacterial, viral, protozoan and helminth gastrointestinal pathogens in children <5 years of age (composite primary outcome) Concentration of intestinal inflammation markers representing environmental enteropathy in children <5 years of age Diversity and abundance of AMR genes in gastrointestinal microorganisms of children <5 years of age (composite primary outcome)			X	
**Secondary outcomes**				
***Physical Health Measures***				
Blood collection for haemoglobin and blood inflammatory markers, children <5 years				X
Anthropometry measures (length-for-age, weight-for-age and weight-for-length z-scores) measure, children <5 years of age				X
***Surveys: Household and community demographic, health and well-being***				
Household members and demographics				X
Household member behaviours and exposures			X	
Access to sanitation, water and hygiene facilities*				*
Caregiver-reported acute symptoms (diarrhoea, respiratory infections and febrile illness), children <5 years of age		X		
Healthcare system utilisation, children <5 years of age		X		
Self-reported or caregiver-reported acute symptoms, healthcare system utilisation and subjective general health (5-point rating scale) among adults and children 5–15 years			X	
Caregiver assessed quality of life (Paediatric Quality of Life Inventory, PedsQL, emotional functioning dimension), children 5–15 years			X	
Self-reported life satisfaction—multiple domains (10-point rating scale), adults			X	
Centre for Epidemiologic Studies Depression Scale (CES-D-10), adults				X
Self-reported major adverse life events, adults			X	
Time-use surveys, children 5–15 years and adults*				*
Housing tenure+ and collective efficacy (Likert 5-point scales)				X
Indicators of household assets and expenditure*				*
Intermittent qualitative surveys and focus groups	NA			
***Measures of environmental faecal contamination***				
Soil and water (potable, recreational, wastewater) samples and animal scat samples for chemical and microbiological analyses (including markers of faecal contamination; prevalence, diversity and concentration of pathogens; abundance and diversity of AMR genes)			X	
***Ecological measures and biodiversity***				
Indoor and outdoor thermal data logging	X			
Passive acoustic monitoring	X			
Aerial and satellite imagery				*
Flood and rain gauges†				X
Mosquito trapping		X		
Rodent trapping†				*

*First and final years of study.

†Indonesia baseline survey only.

A, annual; AMR, antimicrobial resistance; B, biannual; C, continuous; Q, quarterly.

### Public involvement

Members of enrolled communities are involved in the design and conduct of this trial, including the design and implementation of the intervention as described above.

## Outcomes

### Primary outcomes

We define our first primary outcome as the prevalence and diversity of bacterial, viral, protozoan and helminthic gastrointestinal pathogens in children under 5 years. Additional primary outcomes are (1) the abundance and diversity of AMR genes in gastrointestinal microorganisms of these children; and (2) the concentration of intestinal inflammation and permeability biomarkers in stool representing environmental enteric dysfunction.

We will use various molecular approaches to assess the presence and concentration of pathogens, microbial communities and AMR genes in human faecal samples. As indicated below, the same methodologies will be applied for processing of environmental samples, thereby optimising assessment of the impact of the intervention on both environmental and human health outcomes. Total nucleic acids will be extracted from faecal samples in-country. Pathogen levels in samples will be measured by quantitative PCR (qPCR) using TaqMan Array Cards^67 68^ targeting >30 bacterial, viral, protozoan and helminthic pathogens. rRNA gene amplicon sequencing will measure microbial biodiversity. Shotgun metagenomic sequencing will be used to gain information about the functional capabilities of pathogens in samples, including the classification and enumeration of AMR genes. Additionally, over 80 AMR genes will be directly detected by qPCR. Expected environmental enteric dysfunction serological markers include faecal myeloperoxidase,^69^ faecal α-1-antitrypsin^70^ and faecal neopterin.^71^

### Secondary outcomes

#### Human health secondary outcomes

Secondary health outcomes include caregiver-reported and self-reported acute symptoms, healthcare utilisation, inflammatory markers in blood, haemoglobin levels and anthropometry measures. Caregiver-reported and self-reported symptoms will be collected via standardised questionnaires throughout the trial, including the presence of diarrhoea, respiratory and undifferentiated febrile illness over the 7 days prior to the survey visit.^72^ Symptoms will be assessed quarterly in children under the age of 5 years and every 6 months in children between 5 and 15 years of age and adults. In all cases, diarrhoea is defined as ≥3 loose or watery stools in a 24-hour period. Healthcare utilisation (visitation to healthcare provider, hospitalisation, antibiotic use) by children under 5 years of age within the 3 months prior to the visit will be surveyed quarterly; for children 5–15 years of age and adults, surveys will be 6 monthly.

Blood from children under 5 years of age will be taken annually by venipuncture. Haemoglobin levels will be measured in the field using a point-of-care device. Plasma and whole blood will be stored for further analyses, which will include markers of nutrition and inflammation. To obtain length-for-age, weight-for-age and weight-for-length z-scores in children under 5 years of age, trained staff will follow standard procedures for anthropometric measurements.^73^ Pairs of trained anthropometrists will measure standing (in children between 2 and 5 years of age) or recumbent (less than 2 years of age) length (accurate to 0.1 cm) and weight without clothing (accurate to 0.1 kg) in triplicate. In both cases, the median of the three measurements will be used in the analysis.^74^

#### Community and individual well-being secondary outcomes

Secondary outcomes related to individual and community well-being include self-reported general and emotional well-being, time-use, measures of collective efficacy and water security, and indicators of socioeconomic status. We will assess the subjective general health and emotional well-being of children aged 5–15 years using the (parent-proxy) Paediatric Quality of Life Inventory 4.0 Emotional Functioning Scale (PedsQL).^75^ Subjective general health, life satisfaction and major life events (ie, family death, serious illness, marriage break-up, bankruptcy, victim of crime) of adults will also be collected 6 monthly.^76 77^ Child (age 5–15 years) and adult time-use (eg, minutes/hours spent on different activities in past week) will also be collected. Gender aspects will be examined, including analyses of sex-disaggregated schooling attendance and the intervention’s impacts on water collection time and well-being for females in our sample. We will assess collective efficacy to monitor changes in community well-being, trust and feelings of safety.^78^ Indicators of socioeconomic status (ie, education levels, house building materials, assets owned, bank account, primary activity, time spent working and subjective financial well-being) will also be collected to facilitate distributional analyses of any observed impacts. We will also estimate the costs of the intervention and report on cost-effectiveness and costs-benefits.

#### Ecological and environmental secondary outcomes

Secondary outcomes for environmental effects include quarterly chemical and microbiological measures to assess faecal contamination of both soil and water (municipal supply, recreational and wastewater), quarterly measures of vector abundance, and continuous measures of the thermal environment and overall biodiversity. We will compare faecal contamination in water and soil samples across intervention and control settlements. Sample collection and transport will be performed using previously described and optimised methods^79 80^ and processed for faecal bacteria quantification.^81^ Nucleic acid extraction will be performed in-country via methods that enable simultaneous detection of viruses, bacteria, protozoa and helminths from environmental samples, as confirmed through optimisation experiments already performed. As with human faeces, pathogen presence and concentrations in samples will be measured using TaqMan Array Cards^67 68^ and AMR markers will be detected by qPCR and shotgun metagenomic sequencing. rRNA gene amplicon sequencing will be performed to determine microbial community composition and diversity.^82 83^ The amplicon outputs will also be used for microbial source tracking using the SourceTracker tool.^84 85^ Changes to the thermal environment will be assessed at the settlement level through remote sensed data supported by local thermal data and compared with changes to the built environment over time.^86^ Continuous temperature tracking will use thermal dataloggers (Thermochron iButtons). Ten randomly selected houses in each settlement will have thermal data loggers installed and a further five thermal data loggers will be deployed across the settlement to measure ambient temperature and humidity. Rainfall data will be derived from multiple (where available) local government-maintained weather stations enhanced with tipping bucket rain gauges installed to maximise coverage across the study area.

We will examine mosquito species variation and abundance over time based on quarterly trapping results. Mosquitoes will be sampled using BG Sentinel II traps^87^ with 15 traps deployed per settlement, inside or outside randomly selected houses. Trap location will remain consistent throughout the assessment period. Mosquitoes will be identified to species under dissection microscopes using morphological keys.^88–90^ Relative abundance and species composition of rodents in communal areas of settlements will also be surveyed in Makassar at baseline using standard traps and a grid-based trapping design to equate trapping effort across sites.^91^ The influence of season and physical environmental features, including temperature, humidity and rainfall, on the relative abundance of vector species will be examined.^92 93^ Continuous passive acoustic monitoring at settlements will provide a measure of overall biodiversity.^94^ The acoustic environment will be monitored using one or two (depending on settlement size) Song Meter SM4 bioacoustic recorders per site for human-audible sound frequencies. Additionally, in Indonesia we will deploy a single Song Meter SM4BAT recorder for ultrasonic frequencies emitted by echolocating bats at each site.

### Referral guidelines

The study will refer participants for treatment to appropriate local healthcare providers in cases of acute malnutrition, anaemia and intestinal helminth infection. WHO weight for length z-scores will be calculated in the field during anthropometry measurements for children under 5 years of age; children meeting WHO/UNICEF criteria for severe malnutrition (weight for length z-score ≤3) will be referred to a local health facility. At times of blood draws, all participating children under the age of 5 years will have their haemoglobin measured in the field. Children with severe anaemia (haemoglobin <7.0 g/dL) will be referred to a local health facility. A subset of faeces samples will be immediately assessed for helminths using the Kato-Katz technique, and individuals with positive results will be referred for treatment.

### Randomisation

Randomisation was performed separately for each city: March 2019 in Makassar and November 2019 in Suva (figure 2). Randomisation occurred following settlement recruitment and completion of 12 months of baseline surveys. Settlements (clusters) have been randomly assigned to either intervention or control groups, with equal numbers in each group. Covariate-constrained randomisation was utilised using the cycrand package in Stata V.15 to achieve balance between the intervention and control groups on key baseline factors determined a priori.

For Makassar, intervention and control groups were first balanced on number of children aged under 5 years (four settlements in each group: ≤10, 11–30 and >30 children) and flood risk (high and low, six settlements in each), producing 90 allocations. Subsequently, the 30 allocations most imbalanced on average asset score were removed, with the score determined from each household’s ownership of selected assets. For Suva, intervention and control groups were first balanced on number of children aged under 5 years (<40 children, eight settlements; >40 children, four settlements) and flood risk and site contamination grouping (two extreme risk, two high risk, and eight medium risk settlements). This resulted in 120 allocations, from which the 30 most imbalanced allocations of asset score were removed, followed by the 30 most imbalanced allocations of average number of children under 5 years. For each of the cities, this resulted in the 60 best balanced allocations being used for the randomisation (total 3600 (60×60) possible allocations for the trial). A randomisation ceremony was held in both cities, where a child from the pilot community selected a ping pong ball from a large glass jar that contained 60 ping pong balls numbered 1–60, representing the 60 determined random allocations that achieved the balance criteria specified above.

### Sample size

The choice of 12 settlements per city, each of ~55 dwellings with five to six people per dwelling, has been made to balance the need for statistical power with the constraints of construction logistics and cost. Statistical power was calculated using formulae for cluster RCTs with repeated assessments of a cohort^95^ (and confirmed by numerical simulation using generalised linear mixed models) for the three primary health outcomes assessed in children aged under 5 years: (1) prevalence of gastrointestinal pathogens and diversity (number of bacterial, viral and parasitic gastrointestinal pathogens per sample); (2) diversity and abundance of AMR markers and (3) concentration of intestinal inflammation markers. For measures of diversity and abundance of markers of drug resistance in environmental samples, the power calculations assumed the same intracluster correlations as for the health outcomes (see below).

For the health outcomes involving subsampling of an average 30 children under 5 years of age per settlement, there is 80% power to detect, from 6-month postconstruction and beyond, a 40% relative reduction in the prevalence of gastrointestinal pathogens (assuming a baseline prevalence of 25%) and a 31% relative reduction in the average count of enteric pathogens per child (assuming a baseline average count of 1.0 and overdispersion factor of 2; with a baseline of 2.0 the relative reduction is 23%), and at 12 months an absolute difference of 0.30 SDs (and 0.34 SDs for environmental assessments) in the average concentration of intestinal inflammation markers and average number and abundance of AMR markers. These calculations assume intracluster (ie, within-settlement) correlations between: two children within the same time period 0.10^7^; two children in different time periods 0.067; and repeated measurements of the same child 0.10. The relative reduction of 30% has been informed by the findings reported in systematic reviews, which have found reductions of 30%–50% due to water quality interventions.^96 97^

### Statistical analyses

Analyses will be by intention to treat. Descriptive statistics will report characteristics of settlements and of individuals by randomised arm. Estimation of the effects of the intervention for each outcome will use generalised estimating equations with an exchangeable correlation structure and robust standard errors clustered at settlement level, scaled with a small-sample degrees-of-freedom adjustment.^98^ Data from 6-month, 12-month, 18-month and 24-month follow-up visits will be included in the analysis and the intervention effect estimated for the 6-month follow-up timepoint for prevalence and mean number of gastrointestinal pathogens, and at 12-month follow-up for diversity and abundance of AMR markers and for intestinal inflammation markers. For binary and count outcomes, we will use a logarithmic link to estimate ratios of prevalence and mean counts, respectively; for continuous outcomes, the identity link will be used to estimate differences in means. All models will adjust for the baseline covariates, number of children under 5 years, flood risk category (see Randomisation section) and asset score. To enable temporal adjustment, indicator variables for seasonal patterns (eg, rainy vs dry), local rainfall data for each site and an indicator term for any major flood event at a particular settlement in a particular quarter will be included in the models. For households that drop out of the study, we will employ multiple imputation using imputation models that preserve the hierarchical data structure. Additional sensitivity analyses will exclude households who moved into the settlement postconstruction. There will be no adjustment to the p values for the assessment of multiple primary health outcomes; however, all findings will be fully reported and interpreted based on incremental evidence.

We will explore relationships between environmental changes and health outcomes by modelling health outcomes at 12-month, 18-month and 24-month postconstruction, using changes in environmental measures at 6-month, 12-month or 18-month postconstruction, respectively, as principal covariates. We will estimate these effects using generalised estimating equations with preconstruction health and environmental parameters as baseline covariates aggregated at settlement-level and will include interactions of environmental changes with the intervention for effect-modification assessment, together with adjustment for potential confounders.

Laboratory technicians conducting sample analyses will be blinded to the intervention assignment throughout the study duration through the use of barcodes for sample identification. Owing to the nature of the intervention, community participants will not be blinded.

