**Methods and analysis:**

RISE is a cluster randomised controlled trial among 12 settlements in Makassar, Indonesia, and 12 in Suva, Fiji. Six settlements in each country have been randomised to receive the intervention at the outset; the remainder will serve as controls and be offered intervention delivery after trial completion. The intervention involves a water-sensitive approach, delivering site-specific, modular, decentralised infrastructure primarily aimed at improving health by decreasing exposure to environmental faecal contamination. Consenting households within each informal settlement site have been enrolled, with longitudinal assessment to involve health and well-being surveys, and human and environmental sampling. Primary outcomes will be evaluated in children under 5 years of age and include prevalence and diversity of gastrointestinal pathogens, abundance and diversity of antimicrobial resistance (AMR) genes in gastrointestinal microorganisms and markers of gastrointestinal inflammation. Diverse secondary outcomes include changes in microbial contamination; abundance and diversity of pathogens and AMR genes in environmental samples; impacts on ecological biodiversity and microclimates; mosquito vector abundance; anthropometric assessments, nutrition markers and systemic inflammation in children; caregiver-reported and self-reported health symptoms and healthcare utilisation; and measures of individual and community psychological, emotional and economic well-being. The study aims to provide proof-of-concept evidence to inform policies on upgrading of informal settlements to improve environments and human health and well-being.

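### The stated 80% power does not belong to the stated primary analysis: an effect estimated at one follow-up visit, without baseline-outcome adjustment, has about 37–40% power for pathogen prevalence

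*Protocol article*

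**What the plan says.** The Sample size section of the protocol article uses formulae for cluster trials with repeated measurement of a cohort, which it says were checked by mixed-model simulation. For the first primary outcome it states that "there is 80% power to detect, from 6-month postconstruction and beyond, a 40% relative reduction in the prevalence of gastrointestinal pathogens", from 25%. It adds a 31% reduction in mean pathogen count (mean 1.0, overdispersion 2; 23% if the mean is 2.0) and, at 12 months, 0.30 SD for inflammation and AMR markers. It assumes "subsampling of an average 30 children under 5 years of age per settlement" and correlations of 0.10 for two children in the same period, "two children in different time periods 0.067; and repeated measurements of the same child 0.10". It does not give the number of baseline or follow-up rounds behind the calculation.

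The Statistical analyses section puts the 6-, 12-, 18- and 24-month data into a GEE, with "the intervention effect estimated for the 6-month follow-up timepoint for prevalence and mean number of gastrointestinal pathogens" and at 12 months for AMR and inflammation. The listed adjustments are number of children under 5, flood risk, asset score, and season, rainfall and flood terms. No baseline measurement of the outcome is listed for these models. The exploratory environment–health models later in the same section do include preconstruction health values.

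**The concern.** The two sections describe effects of different precision. A calculation based on repeated assessments gains from averaging visits and from the correlation with baseline. An effect at one visit loses the first gain, and a model without the baseline outcome loses the second. If every child is seen at every visit and each visit has its own arm effect, the 6-month estimate is essentially the difference between the 6-month means, and the later visits add almost nothing to it.

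At stake is how the main result is read. Run as literally written, and before any covariate gain, the first primary outcome would more often than not miss the reduction the trial was sized for. A null 6-month result would then be judged against a published 80%, in a trial meant to inform settlement-upgrading policy.

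**Working it through.** **Inputs from the protocol.** "RISE is a cluster randomised controlled trial among 12 settlements in Makassar, Indonesia, and 12 in Suva, Fiji"; settlements allocated "with equal numbers in each group", so 12 per arm; 30 children per settlement; correlations 0.10 (same period), 0.067 (different periods) and 0.10 (same child). Targets: 25% to 15%; mean count 1.0 to 0.69 with variance twice the mean; 0.30 SD.

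**Assumed, because not stated.** Two-sided 5% alpha; 22 df where a t reference is used; no dropout; equal settlement sizes.

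**Variance of a settlement mean (SD units)**
- One visit: (1 + 29×0.10)/30 = 0.130
- Covariance between two visits: (0.10 + 29×0.067)/30 = 0.0681
- Mean of four visits: (0.130 + 3×0.0681)/4 = 0.0836
- Mean of four visits adjusted for one baseline round: 0.0836 − 0.0681²/0.130 = 0.0479
- One visit adjusted for one baseline round: 0.130 − 0.0681²/0.130 = 0.0943
- One visit adjusted for the mean of two baseline rounds, whose variance is (0.130 + 0.0681)/2 = 0.0991: 0.130 − 0.0681²/0.0991 = 0.0832

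With V the relevant variance, power = Φ(difference/SE − 1.96), where SE² is:
- prevalence: (0.25×0.75 + 0.15×0.85)×V/12 = 0.315×V/12
- log count ratio: (2/1.0 + 2/0.69)×V/12
- continuous: 2×V/12

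**Reproducing the plan's figure.** With V = 0.0479, the prevalence SE is √(0.315×0.0479/12) = 0.0355. Then 0.10/0.0355 = 2.82 and power is 80.5%, matching the stated 80%. The same design gives about 76% for the 31% count reduction, 78% for the 23% reduction and 92% for 0.30 SD. The 0.30 SD figure is matched by one baseline round and the mean of two follow-ups (79.7% with t). No single design returns every stated figure. Over 0–2 baseline rounds and 1–4 follow-ups, every variant reaching 80% uses both a baseline round and an average of visits.

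**The analysis as written: one visit, no baseline outcome, V = 0.130**
- Prevalence: SE = 0.0584; 0.10/0.0584 = 1.71; power 40% (37% with t)
- Count: SE = 0.230; −ln 0.69 = 0.371; ratio 1.61; power 36%
- 0.30 SD: SE = 0.147; ratio 2.04; power 53% (50% with t)

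Detectable at 80% power (normal approximation): about a 61% reduction in prevalence, about 50% in count, and 2.80×0.147 = 0.41 SD.

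**Other readings (normal approximation, before covariate gain)**

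| Analysis | V | 25% to 15% | 31% count | 0.30 SD |
|---|---|---|---|---|
| One visit | 0.130 | 40% | 36% | 53% |
| One visit, one baseline round | 0.0943 | 52% | 47% | 67% |
| One visit, two baseline rounds | 0.0832 | 57% | 52% | 72% |
| Common effect, four visits | 0.0836 | 57% | 52% | 72% |
| Four-visit mean, one baseline round | 0.0479 | 80.5% | 76% | 92% |

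**Covariate gain.** Let stable settlement covariates remove a share s of the 0.10 between-settlement variance.
- One visit: V = 0.130 − 0.10s. At s = 0.5, V = 0.080 and power is about 59% (prevalence) and 74% (0.30 SD). Reaching 80% needs s of about 0.81 and 0.61.
- Common effect over four visits: V = 0.0836 − 0.10s. An s of about 0.35 gives 80% for prevalence, and about 0.15 gives 80% for 0.30 SD.

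**The case against.** The strongest reply is that the single-visit reading is not the only one. All four visits enter one model, no arm-by-visit term is named, and the power statement speaks of 6 months onward, so a common effect might be intended. The planned covariates are also those used to constrain the randomisation and may explain real variance. Baseline-outcome adjustment might appear in an analysis plan that is not shown.

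Much of this stands as a limit on precision. A reader might infer that power is simply 40% for prevalence and 53% for 0.30 SD. The documents do not support those as fixed values, because both give the covariates no credit and take the least favourable reading. The 0.30 SD part is the less secure: both sections say 12 months, and on the common-effect reading a modest covariate gain would reach 80%.

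A reader might also infer that the sponsor's calculation demonstrably assumed four pooled visits and one baseline round. That is only an inference from the prevalence figure, since the cited formulae and the simulation are not visible and no one design fits all the targets. Nor can a specific further loss for unequal settlement sizes be claimed. The Makassar strata ("four settlements in each group: ≤10, 11–30 and >30 children") show that sizes vary, but not by how much.

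The reply does not rescue the stated 80%. The text names a timepoint for the effect, and on the common-effect reading prevalence is still at 57% before covariate gain. The article does list the primary model's covariates, and the baseline outcome is not among them.

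**Conclusion.** The point holds: the 80% in Sample size is not the power of the analysis in Statistical analyses. For the effect as literally stated, power is about 37–40% for prevalence, 36% for the count and 50–53% for 0.30 SD. The common-effect reading gives about 57%, 52% and 72%. All these figures precede covariate gain. On the single-visit reading, the covariates would have to remove about 81% of the between-settlement variance to bring prevalence to 80%, and the protocol claims nothing of that kind. The conclusion is firmest for prevalence and counts and weaker for 0.30 SD. It rests on the protocol's own correlations and cluster numbers, an assumed two-sided 5% alpha, equal settlement sizes and complete data.

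**What to change.** 1. Reconcile the two sections. State for each primary outcome whether the effect is specific to a visit or common to the follow-up visits, and use the same definition in the power paragraph.
2. Add the settlement-level baseline value of the outcome to the primary models. The protocol describes a completed 12-month baseline period and stool collection at least twice a year, so this should need no new data. On its own it brings a single-visit prevalence effect only to about 52–57%.
3. Restate power and detectable differences for the effect that is kept, as a range over plausible covariate gain, giving alpha and the number of baseline and follow-up rounds. If the single-visit effect is kept without baseline adjustment, the starting values before covariate gain are about 61%, 50% and 0.41 SD.

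Alternatively, the sponsor could make the baseline-adjusted average over the follow-up visits primary and report visit-specific effects as secondary. That recovers about 80% for prevalence, but the headline result becomes an average over follow-up rather than an early effect. This changes the estimand and is the sponsor's choice.

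The cost is revised wording in the analysis section and a recalculated power paragraph.
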